### Participants

All children enrolled in grade 4, i.e., about 9 to 11 years of age, are eligible for participation. This grade is selected because of children‘s ability to comprehend the questionnaire items and their availability during follow-up assessment (children should not have made the transition to secondary school before the 2nd follow-up assessment is completed). To account for a lower response rate, 40 students in grade 4 will be stratified by gender and then randomly selected. Although our target sample is of at least 13 teachers per school, all teachers in the selected schools will be included in the study sample. Both children and teachers will be assessed at pre-assessment (baseline) and the two follow-up assessments, 6 months, and 18 months after the interventions.

### Assessment Procedures

As part of the recruitment process, the implementing partner—P4H Global, a Haitian NGO providing training programs to teachers in Haiti—will visit the selected 36 schools to advertise the study, meeting first with the school principals. These visits serve to check the inclusion criteria for schools and to ensure the willingness of principals to participate in the study.

The local partner will shortly return to schools to register and enroll the teachers and the children. To ensure common and clear understanding of the relevant details of the study, the local partner will provide information to selected students and voluntarily participating teachers in a formal information session. Parental informed consent will be sought for each selected student through information sessions for parents at the school or through letters sent out to parents. After baseline, schools will be allocated into treatment and control groups, and the program will be delivered to those in the treatment group after the baseline (pre-) assessment is completed.

Data will be collected from both control and treatment schools. Both teachers and children will be surveyed. Data collection will take place in three stages: (i) t_0_, at baseline – before the intervention; t_1_, 6 months after the intervention; and t_2_, 18 months after the intervention. Each data collection phase will take approximately two and a half months. Data will be collected using tablet-based surveys and the software Survey-to-go (22). Since floor effects were detected in the feasibility study, surveys will not be self-administered but conducted as interviews in Haitian Creole. A team of enumerators (external to the local partner facilitators so that results are not contaminated) will be trained in the use of this survey methodology and the collection of data. The local partner leadership will recruit and supervise the enumerators, who will be trained prior to the implementation of the program by the research team. Enumerators should be native Haitians, fluent in both English and Haitian Creole and ideally have a background in psychology, pedagogy, education, or related disciplines. The local partner and the research team will provide onsite supervision structure to this team of enumerators through the duration of the study. Enumerators will be blind regarding the allocation of the schools.

Children whose parents provided informed consent and who themselves consented to participate will be interviewed by the enumerators within the school premises. To guarantee privacy, the children will be seated in such a way that no one can hear how they answer to the questions. Teachers who agree to participate and provide informed consent will be interviewed during breaks between school lessons (or after work at school). When acquiring participants' informed consent, enumerators emphasize that participants can withdraw from the study at any time without any negative consequences and that, if they decide to do so, they can object to the use of their previously collected data. Interviews will take (on average) 45 min for teachers and 60 min for children at baseline and at the follow-up assessments. In addition, children will participate in a standardized numeracy and literacy testing and a cognitive assessment at each time point.

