### Intervention Procedures

Each ICC-T training workshop will be delivered by two main facilitators with the assistance of one assistant facilitator. All facilitators are trained Haitian teachers, education specialists, and psychologists. They had already been certified by the research team as ICC-T facilitators. They will receive a series of refreshing training sessions from the research team before the delivery of the ICC-T to treatment-condition schools. All the materials for conducting the ICC-T sessions will be available in Haitian Creole, similarly all the presentations and discussion meetings during the workshop will be held in this language.

The ICC-T training workshop will be scheduled by our local partner, P4H Global, according to the current school calendar so that teachers have time to attend the 5 days of the workshop. All teachers who are employed at the treatment schools will be eligible to participate in the training. Participation in the training will be voluntary and free of charge. The local partner will provide food and beverages to participants as well as transport compensation (6 USD per person). Prior to their participation in the training, teachers will be given introductory (consent) forms, informing them of the voluntary nature of their participation as well as their right to withdraw from the training at any point. Teachers who have agreed to participate will sign the training informed consent form. The research team will ensure that the information shared during the workshop sessions remains confidential. No personal information will be disclosed to external sources.

Of the at least 36 schools that will participate in the study, the local partner will deliver the ICC-T program to half of the schools (at least 18). Workshop sessions will take place in 2 rounds. In the first round, at least 10 schools (about 130 teachers) will be trained. In the second round, at least 8 schools (about 104 teachers) will be trained. Each round of trainings will consist of five ICC-T trainings taking place in different locations. A total of 9 workshops (2–3 schools per workshop, maximum 30 participants per workshop) will be delivered by the local partner's trained staff. As one workshop takes 5 days and multiple workshops can be delivered by the local partner at the same time, all workshops can be delivered within a time window of about 1 month.

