### Measures Against Bias

To minimize recruitment bias, a stratified random sampling approach is used. To minimize bias from using unvalidated outcome measures, a careful selection of the assessment instruments has been undertaken. Since the school allocation will be executed at the cluster level and by independent researchers, the data collectors will be blind to the treatment conditions of the schools. To further minimize the risk of contamination between treatment conditions, there will be no contact between the intervention facilitators and data collectors. Although the intervention participants will not be blind regarding whether they belong to the treatment or the control group, the use of violence by teachers will also be assessed through children's self-reported exposure to violence. To avoid incomplete accounting of participants and outcome events, the analysis will treat groups as randomized (“intention to treat”).

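### The partner that delivers ICC-T, and knows every school's arm, also recruits the enumerators and co-supervises them on site; the safeguards separate enumerators only from the facilitators

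*Protocol article*

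**What the plan says.** Under Assessment Procedures the local partner is introduced as "the implementing partner—P4H Global, a Haitian NGO providing training programs to teachers in Haiti". Under Intervention Procedures "the local partner will deliver the ICC-T program to half of the schools": it schedules the workshops, which "will be delivered by the local partner's trained staff", and it provides teachers' food and transport compensation. Under Control Schools it keeps in close contact with the untrained schools for the whole study.

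The same organisation has a role in measurement. Assessment Procedures state "The local partner leadership will recruit and supervise the enumerators" and "The local partner and the research team will provide onsite supervision structure to this team of enumerators through the duration of the study". The enumerators interview teachers and children, and so collect both primary outcomes.

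Two safeguards bear on this. Enumerators are to be "external to the local partner facilitators so that results are not contaminated" (Assessment Procedures), and "there will be no contact between the intervention facilitators and data collectors" (Measures Against Bias). The article also states that enumerators are blind to allocation, that the research team trains them, and that independent staff carry out the allocation.

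**The concern.** Both primary outcomes are self-reports taken face to face, so they depend on what respondents think the interviewer wants and on what the interviewer knows. The article accepts that teachers are unblinded (Measures Against Bias). It also accepts that their reports may err in the direction of the intervention effect, and it expects social desirability to matter (Discussion). It applies the principle of keeping programme and measurement apart, but only to the people who run the workshops.

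The remaining gap is at the level of the organisation. Enumerators answer in part to people who know every school's arm, and no rule says how that knowledge is kept from them. Treated teachers have spent five days with the partner and received food and transport money from it. If they connect the interview with that organisation, they have a reason to under-report that control teachers share to a lesser degree. A difference of this kind looks like a treatment effect, and it cannot be separated from one in the analysis once the follow-up data are in.

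**Working it through.** **Which safeguard covers whom**

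| Group | Knows the arm? | Separated from enumerators? |
|---|---|---|
| Workshop facilitators (partner staff) | Yes, they deliver the training | Yes: external to them, and no contact |
| Partner leadership | Yes: the partner schedules the workshops and monitors control schools | No: recruits and supervises enumerators |
| Partner site supervisors | Their organisation does; no rule keeps it from them | No: on site, jointly with the research team |
| Research team | Not stated | Not applicable: trains and co-supervises |

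The second and third rows are the gap.

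**Scale, under an assumption.** The article gives no estimate of a reporting shift. The calculation below shows only how sensitive the teacher test is to one.

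Inputs from Power Calculation: 36 schools, 13 teachers per school, 30% teacher dropout, alpha 0.05 (taken as two-sided), teacher effect 0.35, R = 0.30. The teacher ICC appears as 0.05 in the text and 0.03 in the parameter list, so both are used. Teachers analysed per school: 13 × 0.70 = 9.1.

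Formula: SE = √{4 × [ICC × (1 − R²) + (1 − ICC)/m] / K}, tested with a noncentral t on K − 2 = 34 degrees of freedom.

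*The plan's own figure first.* Taking 0.30 as the share of school-level variance explained:
- Students: m = 28 × 0.75 = 21, ICC 0.03, effect 0.25. SE = √{4 × (0.021 + 0.97/21)/36} = 0.0864; power 80.3%.
- Teachers: m = 9.1, ICC 0.03, effect 0.35. SE = √{4 × (0.021 + 0.97/9.1)/36} = 0.1191; power 81.5%.

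Both give 36 as the smallest even number of schools with at least 80% power, so the formula reproduces the plan.

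*No true effect, pure reporting shift in treated teachers.* With ICC 0.05, SE = √{4 × (0.05 × 0.70 + 0.95/9.1)/36} = √{4 × 0.1394/36} = 0.1245. Probability of a significant result:

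| Assumed shift (SD) | Share of 0.35 | ICC 0.05, explained share 0.30 | Range over ICC 0.03 or 0.05 and explained share 0.09 or 0.30 |
|---|---|---|---|
| 0 | 0% | 5% | 5% |
| 0.05 | 14% | 6.8% | 6.6–6.9% |
| 0.10 | 29% | 12.2% | 11.7–12.9% |
| 0.15 | 43% | 21.6% | 20.4–23.2% |

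(0.09 is 0.30², for a reader who takes R as a correlation.) The choice of ICC and R hardly matters; the assumed shift drives the result.

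No such figure is given for child report. Children did not attend the workshops, and nothing in the article supports giving them the same shift.

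**The case against.** The strongest reply is that neither stated safeguard is breached. Both concern facilitators, and nothing says that leaders or site supervisors also facilitate. This stands. A reader might infer that the promised separation fails, but the documents support only that it stops short of the organisation.

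A reader might also infer that control teachers have no tie to the partner. The article contradicts this: the partner visits all schools, enrols teachers and children, runs the information sessions, and stays in close contact with control schools. The arms differ in degree: treated teachers additionally have the workshop and its hospitality.

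Third, the protections are real. The research team trains the enumerators and shares supervision, allocation is independent, enumerators are stated to be blind, and the Discussion stresses training them to handle desirability. Providing on-site supervision need not mean a partner representative within earshot. These points reduce the risk. They do not say how an allocation known to a co-supervisor stays hidden.

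Fourth, that teachers would answer to please their trainer is inference. The interviewer is not the trainer, and the article does not say how enumerators present themselves. Unblinded teachers may shade their answers whoever supervises, and the article admits this. Only an increment on top of that can be attributed to the partner's role.

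Finally, child report is the stated counterweight, and children are seated so that nobody overhears. A reader might infer equal damage to that outcome; the documents leave only leaked allocation or influence from supervisors as routes. The absence of a matching seating rule for teachers affects both arms and may simply be field-manual detail, so it is an adjunct to the fix and not part of the proof.

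**Conclusion.** The concern holds in a limited form. The implementing organisation, which knows the allocation, recruits the enumerators and co-supervises them on site while they collect both primary outcomes. The safeguards do not extend to its leadership or site supervisors. Enumerator blinding and freedom from differential desirability bias are therefore not fully protected, chiefly for teacher self-report.

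The size is unknown. The range of about 7% to 22% false positives rests entirely on an assumed shift of 0.05 to 0.15 SD confined to treated teachers, with no true effect. It shows sensitivity and does not predict bias. The documents do not show that blinding will fail, that teachers will identify enumerators with the partner, or that supervisors will influence answers. This is an inexpensive improvement to the design and not a fatal flaw.

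**What to change.** In Assessment Procedures and Measures Against Bias:

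1. At the 6- and 18-month assessments, extend the no-contact rule from facilitators to all partner staff who know the allocation, and keep them off school premises on interview days.
2. Let the research team, already co-supervisor, run on-site supervision through lead enumerators drawn from the existing team. Limit the partner to recruiting enumerators before allocation and to logistics.
3. Have enumerators introduce themselves as working for the university and not for the training organisation.
4. Apply to teacher interviews the out-of-earshot seating already specified for children.

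The cost is a changed reporting line, a few sentences in the protocol and enumerator instructions, and some supervision now shared with the partner passing to the research team. The documents do not show whether the research team could take over recruitment as well across three waves of about two and a half months each, so the fix leaves pre-allocation recruitment with the partner. It does not remove teachers' knowledge of their own arm, which remains a limitation to report.

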### Intervention Description

In the treatment condition, ICC-T will be delivered as a 5-day training workshop (9 h per day). Drawing on attachment, behavioral and social learning theories, ICC-T provides teachers with practical information and tools to prevent the use of violent disciplinary strategies in class and to improve their interaction competencies with children. Workshop sessions are divided into five modules (12): (1) improving teacher-student interactions, (2) maltreatment prevention, (3) effective discipline strategies, (4) identifying and supporting burdened students, and (5) implementation of ICC-T components in everyday school life. Sessions about *teacher-student interactions* aim to increase teachers' understanding of children's behavior, raise awareness of their responsibility of being a role model for students and foster positive teacher-student communication and interaction. Sessions on *maltreatment prevention* aim to raise awareness of the negative consequences of violent discipline for children's well-being. Teachers are encouraged to reflect on their own experiences of violent discipline as a child and to connect their own experiences and feelings to their current discipling behavior and its consequences. Sessions on *effective discipline strategies* aim to equip teachers with practical tools on how to maintain and reinforce desired behaviors of students and how to change misbehavior. The sessions on *identifying and supporting burdened students* aim to raise teachers' awareness of common internalizing and externalizing problems of children and to provide strategies how to support children with these problems in the school context. Finally, in the sessions on *implementation* teachers are encouraged to devise ways of how they can apply the ICC-T components in everyday school life and to create long-term support strategies to promote the sustainability of the intervention content.

Throughout the ICC-T sessions, teachers are invited to participate actively and think about how they can implement the workshop's components and acquired skills in their daily work. To create a trusting and open environment, participants are encouraged to discuss openly about their work problems, needs, and prior experiences with violent discipline. To promote sustainability, the workshop includes exercises for practicing, reinforcing, and repeating the workshop's content, activities that promote teachers' self-reflection about their own behavior, team-building measures as well as the organization of a peer consulting system in schools.

### Intervention Procedures

Each ICC-T training workshop will be delivered by two main facilitators with the assistance of one assistant facilitator. All facilitators are trained Haitian teachers, education specialists, and psychologists. They had already been certified by the research team as ICC-T facilitators. They will receive a series of refreshing training sessions from the research team before the delivery of the ICC-T to treatment-condition schools. All the materials for conducting the ICC-T sessions will be available in Haitian Creole, similarly all the presentations and discussion meetings during the workshop will be held in this language.

The ICC-T training workshop will be scheduled by our local partner, P4H Global, according to the current school calendar so that teachers have time to attend the 5 days of the workshop. All teachers who are employed at the treatment schools will be eligible to participate in the training. Participation in the training will be voluntary and free of charge. The local partner will provide food and beverages to participants as well as transport compensation (6 USD per person). Prior to their participation in the training, teachers will be given introductory (consent) forms, informing them of the voluntary nature of their participation as well as their right to withdraw from the training at any point. Teachers who have agreed to participate will sign the training informed consent form. The research team will ensure that the information shared during the workshop sessions remains confidential. No personal information will be disclosed to external sources.

Of the at least 36 schools that will participate in the study, the local partner will deliver the ICC-T program to half of the schools (at least 18). Workshop sessions will take place in 2 rounds. In the first round, at least 10 schools (about 130 teachers) will be trained. In the second round, at least 8 schools (about 104 teachers) will be trained. Each round of trainings will consist of five ICC-T trainings taking place in different locations. A total of 9 workshops (2–3 schools per workshop, maximum 30 participants per workshop) will be delivered by the local partner's trained staff. As one workshop takes 5 days and multiple workshops can be delivered by the local partner at the same time, all workshops can be delivered within a time window of about 1 month.

Treatment fidelity will be monitored in several ways. First, both facilitators will fill out a short purpose-built questionnaire after each session including items on the session's duration, applied methods, and perceived uptake of the session content by participants as well as a checklist on possible deviations from the intervention manual and didactical aspects. Second, at the end of each workshop day, four randomly selected participants will be asked to fill out a purpose-built questionnaire on their perceived understanding of that day's training content and the helpfulness of the applied methods in delivering the content. Third, all participants will be asked to evaluate the training contents and methods using a purpose-built questionnaire at the end of the workshop. Fourth, two independent raters will evaluate video and audio recordings of pre-determined sequences of ~10 min to determine whether intervention workshops were implemented in line with the manual.

### Control Schools

No ICC-T workshops will be delivered to teachers working at control-condition schools. That said, the local partner will have close contact with control schools to ensure that teachers do not receive any training of a similar nature during the total study duration. School (vice)principals should consent to this. Data collection at control schools will be conducted both at baseline (pre-assessment) and in two follow-up phases.

### Study Measures

Following established international guidelines, Haitian Creole native speakers will translate all the forms and measures from English into Creole and then back into English in a blind written form. The back-translated items will then be compared with the original items to verify that the translation has been correctly undertaken and the content is equivalent. To ensure high objectivity and reliability during data assessment, standardized procedures on questionnaire administration will be developed and implemented. All surveys will be undertaken in Haitian Creole. Prior to data collection, a pilot study in one primary school (which will not be included in the trial) will be conducted to ensure the feasibility of the questionnaire administration.

The main outcome measure is teachers' use of violence. This will be measured in two ways: (i) teachers' self-reported use of violence, and (ii) children's self-reported experiences of violence. Secondary outcome measures are teachers' attitudes toward violent discipline, children's mental health problems and quality of life as well as their cognitive performance. Additionally, we will assess children's experiences of peer violence, social competence and their academic performance through a standardized literacy and numeracy test and children‘s scores in Mathematics, Creole-French, Science, Social science, and General Studies in the mid-term. These scores will be provided by the school administration.

